**Fig. 2 Fig2:**
[figure not shown]
Computational biophysical models of an in-house ipsilateral dorsolateral prefrontal (ipsi-DLPFC), contralateral anterior cerebellar lobe (contra-CEREB), and combined prefronto-cerebellar (ipsi-DLPFC + contra-CEREB) tDCS montages were developed in SimNIBS 3.2.3 using a 3D reconstruction of the MNI152 model brain. Electrode positions surrounded by red circles represent active anodes; those surrounded by blue circles, correspond to active cathodes; finally, electrodes surrounded by black circles represent inactive electrodes (placed in the head cap during the stimulation only to ensure the operator’s blinding). **A** Optimized montage solution for the ipsilesional prefrontal target (DLPFC) assuming a left hemisphere stroke. Ag/AgCl $$\uppi {\mathrm{cm}}^{2}$$ electrode position and current intensities are defined by an optimization procedure resulting in the following scalp montage and currents to be delivered (10/20 EEG system): F3 (1.736 mA), F1 (− 1.222 mA), and FC5 (− 0.536 mA). **B** Illustration of the optimized solution for the contralesional anterior cerebellar lobe (CEREB) target assuming a left hemisphere stroke. Ag/AgCl $$\uppi {\mathrm{cm}}^{2}$$ electrode position on the scalp and intensities were automatically defined by an optimization procedure resulting in the following montage (10/20 EEG system): PO10 (1.960 mA), FT10 (− 0.550 mA), CP6 (− 0.180 mA), Oz (− 0.630 mA), and P9 (− 0.631 mA). **C** Final simulation merging DLPFC and cerebellar electrode montages assuming in this specific case a left hemisphere stroke, pertaining to the prefronto-cerebellar stimulated group. All images are presented in terms of total electric field strength (|E|). The visual color impact scale was normalized in all images from a minimum of 0 V/m (blue areas) up to a maximum of 0.36 V/m (red areas). Contra-CEREB: anodal contralesional cerebellum, ipsi-DLPFC: anodal ipsilesional dorsolateral prefrontal cortex, ipsi-DLPFC + contra-CEREB: anodal ipsilesional dorsolateral prefrontal cortex with anodal contralesional cerebellum, normE: electric field strength (|E|)

#### Stimulation procedures

HD-tDCS will be delivered to all experimental groups with a Starstim-8® device, a wireless hybrid EEG/tES 8-channel system (Neuroelectrics, Barcelona, Spain). The Neuroelectrics Instrument Controller® software (NIC) associated with this hardware will be used to pre-program all HD-tDCS and EEG protocols and carry out interventions. Given the four-parallel arms of our study design (ipsi-DLPFC, contra-CEREB, ipsi-DLPFC + contra-CEREB, and SHAM) and considering participants with left or right hemisphere stroke, a total of 8 HD-tDCS protocols will be pre-programmed.

During stimulation sessions, participants will wear a neoprene cap adapted to the circumference of their head ensuring correct placement for NG pistim® electrodes (πcm^2^ surface, Ag/AgCl) embedded in SignaGel® (Parker laboratories, USA) to keep impedances below 10 KΩ. Every participant will receive 10sessions of tDCS, 20 min each and 5 daily sessions per week (Monday to Friday) during 2 consecutive weeks (W1 and W2 of participants’ schedule).

The tDCS device integrates a maximum of 8 electrodes to deliver stimulation. However, note that depending on the experimental tDCS group, different electrodes will be actively involved in stimulation at each condition (see tDCS montage protocol section). To conceal the stimulation condition and preserve the blinding of the operator and the participant, all 8 available electrodes will always be positioned on the participant’s head cap and will have their impedance tested. Crucial values such as mean voltage, current intensity, and impedance of the different electrodes employed will be recorded automatically during the sessions. Targeted regions are represented in Figs. 2 and 3.

**Fig. 3 Fig3:**
[figure not shown]
Transcranial tDCS targeted regions (used for electrode optimization and subsequent stimulation) assuming in the image a left hemisphere stroke. Established MNI (Montreal Neurological Institute) coordinates have been selected ensuring a constant electric field impact (0.25 mA) in Brodmann area 46 for the dorsolateral prefrontal cortex (DLPFC) and lobules  I–IV of theanterior cerebellar lobe (CEREB). **A** DLPFC target area (MNI coordinates *X* =  − 39, *Y* = 34, *Z* = 37) in an axial (*a.1*), coronal (*a.2*) sagittal (*a.3*) MRI sections and their scalp projection (*a.4*) views. **B** Cerebellar target area (MNI coordinates: *X* =  24, *Y* =  − 66, *Z* = 40) in axial (*b.1*), coronal (*b.2*), sagittal (*b.3*) MRI sections and their scalp projection (*b.4*) views. Target areas are represented in the MNI152 and labelled on a standard MRI model by means of an MRI-based frameless stereotaxic neuronavigation system (Brainsight)

#### Active tDCS conditions

Once the head cap is positioned and all the necessary electrodes are attached, the current intensity will be linearly increased (ramp up) for 30 secs to reach the peak current intensities delivered in each specific condition: (1) 1.736 mA intensity (0.55 mA/cm^2^ density) in the ipsi-DLPFC group (receiving ipsilesional prefrontal stimulation); (2) 1.999 mA intensity (0.63 mA/cm^2^ density) in the contra-CEREB group (receiving contralesional anterior cerebellar lobe stimulation); and (3) 3.735 mA intensity (0.55 mA/cm^2^ density in the ipsi-DLPFC area and 0.63 mA/cm^2^ in contra-CEREB) in the ipsi-DLPFC + contra-CEREB condition (receiving simultaneously dorsolateral prefrontal and cerebellar stimulation). Once the predefined intensity is reached, the current will be kept active for 20 min, a treatment duration that has been proven effective in prior studies with neurological patients [14, 15]. Finally, tDCS current will be ramped down for 30 secs at the end of the stimulation session.

During the delivery of tDCS, patients will be seated in a comfortable chair. To keep patients awake and restrict interindividual and intraindividual variability caused by a diversity of neural states present across subjects and sessions, participants will be asked to perform a simple computer-based game on a monitor placed 57 cm in front of them (hence at arm’s reach) requiring keyboard presses (space bar) with their non-impaired hand, every time a moving dot contacts the borders of a centered rectangular placeholder (8 × 13 degrees of angle/cm).

#### Sham tDCS condition

The sham tDCS intervention will follow the same procedure as the active conditions, even though placebo current stimulation will be applied. At the beginning of the session, during the first 30 secs, electrical current will be ramped up emulating the ipsi-DLPFC + contra-CEREB stimulation condition. Immediately thereafter, a 5-secs ramp-down will cease the delivery  of electrical current. During the following 20 min of the session no electrical current will be administered. At the end of the session, the same procedure will be repeated, delivering a 5-secs ramp up followed by a 30-secs ramp down to null intensity. This protocol commonly known as “FISSFO” (Fade In of Stimulation, brief real Stimulation, Fade Out) has been extensively used in clinical trials to mimic during sham conditions the tingling and itching skin sensations perceived during the ramp up and ramp down of tDCS intensity [45]. In the current clinical trial, patients will undergo tDCS treatment during the late subacute to chronic phase following a stroke, hence optimal for non-invasive neuromodulation, but during which, instances of spontaneous recovery might still operate. Moreover, for ethical reasons, while participating in our study, patients will continue their conventional physical rehabilitation program (see next section for details), which *per se* could also contribute recovery. In such circumstances, and also to counter improvement effects caused by familiarization and training in evaluation tasks performed several times during the study follow-up, a sham stimulation group is key to identify genuine recovery fostered by transcranial stimulation.

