## Introduction

Middle cerebral artery (MCA) strokes are known to cause direct structural damage to key sensory-motor networks in charge of executing and controlling voluntary motion actions in frontal and anterior parietal cortical or in associated subcortical structures. Despite the influence of lesion location and extent [1–3], the magnitude of motor performance deficits following stroke [4–6] cannot be solely explained by ischemic damage on motor systems but also by diaschetic effects altering network interactions with local and distant structures contributing substantially to optimal motor activity.

Transcranial direct current stimulation (tDCS) is among the most popular non-invasive brain stimulation approaches currently used in clinical settings. It is characterized by its portability, low cost, ease of use, a safe profile of side effects, and high flexibility to target several locations simultaneously. Transcranial DCS is based on the application of a low-intensity continuous current inducing polarity-dependent sub-threshold shifts of neuronal resting membrane potential towards (anodal) or away (cathodal) from the firing threshold [7–10].

By virtue of such effects, whereas single sessions of tDCS have shown the ability to transiently modulate corticospinal excitability, periodical sessions of such simulation promote long-term potentiation/depression-like plasticity [11]. Transcranial DCS has been used as a therapeutic intervention to boost cognitive and motor recovery following stroke in diverse settings and evaluated with regards to its ability to improve voluntary upper limb function [12–16]. Despite its success in small samples of selected participants, the effects reported by accumulative tDCS interventions in stroke have often been shown to be inconsistent when applied to larger cohorts of patients [17]. Additionally, tDCS outcomes have been found to be highly influenced by variables such as post-stroke-to-treatment-onset time-lag, lesion site and volume, a large variety of stimulation parameters (electrode location, current intensity, density, regime periodicity, etc.), and interindividual head and brain anatomical differences affecting the distribution of tDCS-generated electric fields [18, 19].

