### Inclusion criteria

 The following inclusion criteria have been established as to be fulfilled by potential participants: (1) to have received a diagnosis of supratentorial ischemic or hemorrhagic unilateral stroke supplied by the middle cerebral artery (i.e., encompassing frontal–temporal-parietal regions); (2) to be enrolled in a “live” rehabilitation program in the Rehabilitation and Physical Medicine department of our institution; (3) to be between 18 and 85 years old; (4) to have suffered a stroke within 4 and 12 months prior to enrollment; (5) to have signed the informed consent form.

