### Randomization and blinding

The study will include *n* = 60 patients with chronic MCA stroke, randomly assigned to one of the 4 experimental groups indicated above (ipsi-DLPFC, contra-CEREB, ipsi-DLPFC + contra-CEREB, or SHAM tDCS). A patient randomization algorithm (*MinimPy* software running in *Python environment*, https://sourceforge.net/projects/minimpy/) counterbalancing groups by sex (Woman/Male), age (− 65 years/ + 65 years) and stroke type (ischemic/hemorrhagic) will ensure equivalence for these three variables across the 4 experimental groups. The biased coin method is an algorithm implementing a biased coin minimization algorithm (base probability: 1, allocation ratio 1:1:1:1) [36] for sequential dynamic allocation, in which each new allocation is influenced by the current state of balance across delivered treatments [37].

An independent co-investigator not involved in the recruitment/enrollment of patients, tDCS application or in clinical evaluation will be in charge of patient randomization and condition/group allocation. The groups of patients associated with the four randomized tDCS conditions will be assigned a letter-coded name (Groups A, B, C, or D) providing no clue with regard to the ultimately delivered tDCS strategy. This same code will be used at all times for patient allocation and only an independent co-investigator in charge of randomization/allocation activities will be able to associate each of the codes (A, B, C, and D) to a specific tDCS condition (aka treatment group). Once a patient will be randomly assigned to a condition/treatment group, its code (A, B, C, or D) will be communicated to a team member in charge of stimulation which will simply deliver it blindly in a non-identifiable manner. To search for the potential influence of placebo or nocebo effects, investigators will debrief at the end of the follow-up, with patients and ask them to guess which stimulation group they believed they had been allocated to (allocation perception).

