## Discussion

The current study protocol (*E-Brain*) aims at assessing the immediate and longer-term clinical potential of ten accumulative sessions of anodal high-density tDCS in patients with upper limb motor disability during the chronic phase  of a unilateral middle cerebral artery stroke. The novelty of our protocol is that instead of aiming to directly modulate damaged motor areas or their contralesional homologues, it focuses on assessing the isolated or combined stimulation of two regions such as the ipsilesional prefrontal cortex (DLPFC) and the contralateral anterior cerebellar lobe (CEREB), not directly involved (as premotor and primary motor systems do) in the execution of motor activity, but instead contributing indirectly to such via the modulation of associated cognitive processes.

A high number of prior conventional NIBS stimulation studies using repetitive TMS or tDCS in post-stroke motor dysfunctions have based their interventions on (i) the upregulation (with anodal tDCS, high-frequency rTMS or iTBS patterns) of ipsilesional M1/premotor systems; (ii) the downregulation (with cathodal tDCS, low-frequency rTMS, or cTBS patterns) of spared contralesional M1/premotor systems by virtue of the trans-callosal rivalrous mutually inhibitory  interactions, remapping, reorganizing, or normalizing abnormal excitability levels in lesional and perilesional areas [62]; or (iii) the upregulation of motor control/coordination systems such as the supplementary motor area (SMA) or the cerebellum. Unfortunately, initial enthusiasm for many of these approaches tested in small clinical trials has dwindled due to the lack of consistent effects when evaluated in larger populations of patients, and efficacy remains debated [63]. For this reason, it is paramount to explore and provide proof-of-concept for new treatments based on the manipulation of cortical sites, with the ability to drive improvements by acting on spared 'non-purely motor ' regions indirectly contributing to the recovery of voluntary motion via the modulation of associated cognitive processes and network-synchronization mechanisms.

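### The stated FMA-UE model leaves out time since stroke, although patients labelled chronic enter at 4 to 12 months; this costs precision and protection against chance imbalance

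*Protocol article*

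**What the plan says.** **Population.** The Randomization and blinding section speaks of 60 "patients with chronic MCA stroke, randomly assigned to one of the 4 experimental groups", and the Discussion of "patients with upper limb motor disability during the chronic phase". The inclusion criterion is "to have suffered a stroke within 4 and 12 months prior to enrollment". The Sham tDCS condition section says that "patients will undergo tDCS treatment during the late subacute to chronic phase following a stroke", a period "during which, instances of spontaneous recovery might still operate", and gives this as one reason for having a sham group.

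**Time since stroke as a prognostic variable.** The Introduction states that "tDCS outcomes have been found to be highly influenced by variables such as post-stroke-to-treatment-onset time-lag", among other factors. The Sociodemographic data section lists time since the stroke event among the baseline items collected.

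**Use in design and analysis.** Minimisation is on sex, age (cut at 65 years) and stroke type, which "will ensure equivalence for these three variables across the 4 experimental groups". The Statistical analyses section gives a repeated-measures ANOVA for the Fugl-Meyer Assessment with TIME (three visits) and GROUP (four arms), or a Kruskal-Wallis test if the data are not normal. No covariate is named. The Data analyses section compares sociodemographic data between groups, and no adjustment follows from that comparison. The limitations in the Discussion concede possible imbalance in lesion extent and severity but do not mention time since stroke.

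**The concern.** The protocol identifies a variable that it believes drives the outcome and collects it, then does not use it in the primary analysis. Two things are at stake.

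- **The arm contrasts.** The primary outcome is change in FMA-UE over roughly seven weeks. If natural recovery is faster soon after stroke, patients at 4 months and at 12 months have different expected changes without any stimulation. An unadjusted model leaves that spread in the error term. With 15 per arm, it also leaves any chance difference between arms in time since stroke uncorrected.
- **The conclusion.** A result reported for chronic stroke would not describe the late subacute patients whom the protocol itself says it treats.

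**Working it through.** **Inputs from the protocol.** Four arms of 15 (Sample size), allocated 1:1:1:1. 4 × 15 = 60, which reproduces the stated total. The entry window is 4 to 12 months. No effect size, SD, recovery slope or power figure is given, so none can be reproduced.

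**Assumptions.** Entry times are uniform over 4 to 12 months. Allocation is random with respect to time since stroke. Time since stroke explains 0 to 30% of the variance of FMA-UE change. The recovery slope is 0.25 to 1.0 FMA-UE points per month of difference in time since stroke. The last two are ranges for illustration.

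**Step 1: chance imbalance for one given pair of arms.**
- SD of entry time = (12 − 4)/√12 = 2.31 months.
- SE of the difference in arm means = 2.31 × √(2/15) = 0.84 months; 95% chance range ±1.96 × 0.843 = ±1.65 months.
- Median absolute difference = 0.674 × 0.843 = 0.57 months.
- At least 1 month: z = 1/0.843 = 1.19, about 24% of trials.
- At least 1.5 months: z = 1.5/0.843 = 1.78, about 8% of trials.

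**Step 2: what that does to a contrast.** Shift = slope × difference in mean time since stroke, in FMA-UE points.

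| Slope (points/month) | Median gap, 0.57 months | Gap of 1 month | Gap of 1.65 months |
|---|---|---|---|
| 0.25 | 0.14 | 0.25 | 0.41 |
| 0.5 | 0.28 | 0.50 | 0.83 |
| 1.0 | 0.57 | 1.00 | 1.65 |

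A second route gives the same order of size. Suppose patients below a 6 to 7 month cut gain 2 to 4 points more than later ones (assumed). An imbalance of 4 of 15 such patients then shifts a contrast by 4/15 × 2 = 0.53 to 4/15 × 4 = 1.07 points. If 25 to 40% of patients fall below the cut, a given pair of arms differs by 4 or more in 14 to 19% of trials.

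**Step 3: type I error.** In 40,000 simulated trials with no treatment effect, the unadjusted tests reject in 4.8 to 5.1% over all randomisations. Conditional on a realised imbalance, the picture differs:

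| Variance explained by time since stroke | 10% | 20% | 30% |
|---|---|---|---|
| Pairwise test, that pair differing by more than 1.65 months | 10% | 15% | 21% |
| Four-arm test, worst-balanced tenth of trials, unadjusted | 9% | 11% | 15% |
| Same, adjusted for time since stroke (4,000 trials) | 6% | 5% | 4% |

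The first row applies to about 5% of trials for a given pair. The adjusted row rests on about a tenth of 4,000 trials and is uncertain by about one percentage point.

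**Step 4: precision.** Adjustment multiplies the residual variance by 1 − R². For R² of 10%, 20% and 30%, the standard error of a contrast is multiplied by √0.9 = 0.95, √0.8 = 0.89 and √0.7 = 0.84, a reduction of about 5, 11 and 16%.

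**Step 5: how the covariate must enter.** In a TIME × GROUP model, a main effect of time since stroke moves all three visits of a patient by the same amount. It cancels out of change over time and leaves the TIME × GROUP contrast unadjusted. Only its interaction with TIME, or its use as a covariate in an analysis of change, does the work.

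**The case against.** The protocol raises spontaneous recovery precisely to justify its sham arm. A concurrent randomised control removes average natural recovery, and the usual standard error already allows for chance imbalance. This stands. A reader might infer that uneven natural recovery is liable to be mistaken for a tDCS effect, or that the sham arm works only if the arms happen to match on time since stroke. The documents do not support either reading: there is no systematic bias, and the raised error rates in Step 3 apply only to the minority of badly balanced trials.

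A reader might also judge the imbalance by the two most different arms of the four. On that measure the gap is at least 1 month in 64% of trials and at least 1.5 months in 29%. The key hypothesis, however, concerns named contrasts (combined stimulation against sham and against each single site). For each of these the figures are 24% and 8%.

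The shift in points rests on a recovery difference that the protocol does not give. It is also small beside the improvement of more than 6 points that the protocol calls clinically significant, although that threshold is for change within a patient, not for a difference between arms.

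An analysis plan that is not shown might add covariates, and the trial is a self-declared pilot. Both points temper the severity. They do not remove the concern, because the model is written out here with two named factors and the inconsistent population label is in the text itself. Comparing baseline data between groups may reveal an imbalance but does not correct it.

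Whether time since stroke deserves a minimisation slot ahead of lesion volume or baseline severity is a matter of judgement that the documents do not settle.

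**Conclusion.** The concern holds as a loss of precision and of protection against chance imbalance, together with an inconsistent description of the population. It does not hold as a claim of bias. With 15 per arm and entry times assumed uniform over 4 to 12 months, a given pair of arms will typically differ by about 0.6 months in mean time since stroke. The resulting shift in FMA-UE is probably around 1 point or less. It exceeds that only when the steepest assumed slope meets an imbalance of more than 1 month. The gain in precision depends on how much variance time since stroke explains, which is unknown here. Severity is minor to moderate.

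**What to change.** 1. **Model.** Pre-specify time since stroke, in months, as a covariate in the FMA-UE analysis for all 60 patients. Include its interaction with TIME, or use it as a covariate in an analysis of change. The variable is already collected and the sample size does not change. The cost is one degree of freedom in an analysis of change, or three in the repeated-measures model (one for the main effect, two for the interaction with three visits). The Kruskal-Wallis fallback as written cannot carry a covariate, so the plan should say how adjustment is kept if normality fails.
2. **Wording.** In Randomization and blinding and in the Discussion, describe the population as late subacute to chronic (4 to 12 months), matching the inclusion criterion and the Sham tDCS condition section. This costs nothing and makes the conclusion fit the patients enrolled.
3. **Optional.** Time since stroke could be added as a minimisation factor for patients still to be randomised; 11 of the planned 60 had completed at the time of writing. Changing the allocation scheme during the trial is debatable, and the covariate delivers most of the benefit without it.
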